Review studies have revealed promising results regarding the effectiveness of braces in treating AIS. However, there is insufficient scientific evidence to recommend their use [9], probably due to the low adherence rates associated with brace use, which tend to be exaggerated when retrospectively evaluated [1]. Adherence to the use of the brace is in fact one of the most important factors negatively influencing the effectiveness of this orthopedic treatment [10]. Two factors that have been argued to explain non-compliance with these orthopedic treatments are (a) the appearance of unwanted effects associated with the use of braces (e.g., pain, scuffing, or discomfort sleeping) and (b) the psychological distress and general beliefs related to the deformity (i.e., “I don’t care about my back”) and its treatment (i.e., “I think people can see the brace under my clothes”) [11,12]. Different efforts have been conducted to improve the adherence to the brace. For example, brace monitoring has been proposed to improve brace compliance [13]. For this reason, it has been argued that there is a need to actively involve patients during the whole treatment process [14], including monitoring of outcomes and brace compliance [1].

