Traditionally, brace adherence has been explored retrospectively [15]. This is problematic because it does not guarantee the security of the treatment, it does not provide reliable data, and it is an inefficient methodology. First, retrospective assessments do not allow the detection of undesired events in the real context and when they occur, but later when patients have a face-to-face medical appointment. As a consequence, the patient must decide what to do when they experience unwanted side effects [16], which compromises the safety of the intervention. For example, an adolescent may decide to immediately stop wearing the brace when they experience pain or itching and therefore would not receive treatment until the next appointment at the clinic (which can occur weeks or months later, depending on waiting lists). Conversely, another patient may decide to tolerate the discomfort and continue wearing the brace despite unwanted side effects until the next appointment with their doctor, which can lead to undue suffering. Therefore, leaving the decision on when and in the presence of which symptom adolescents should respond to and how they should respond can be problematic. Regarding the second point, which refers to the reliability of the data, research has shown that retrospective assessments are not free from recall bias. In particular, more severe symptoms tend to be reported when health conditions are retrospectively assessed [17]. In the specific case of brace monitoring, it is unlikely that patients will be able to remember the exact number of hours and days that they have been wearing the brace for a given period of time. It is also unlikely that adolescents will be able to remember all the side effects they experienced in the different contexts in which they occurred. The latter point refers to treatment efficiency. Retrospective evaluations are not efficient as they do not allow early detection of noncompliance with brace treatment and psychological distress related to brace use (i.e., irrational beliefs, intense unpleasant emotions, or lack of social support). Therefore, early interventions cannot be delivered in response to these, which means that the patients’ quality of life may be affected. This, in turn, could result in more lasting and severe symptoms (i.e., brace-related side effects, anxiety, and depressive symptoms), ultimately resulting in higher personal and financial costs (i.e., recurrent visits and contacts with health services).

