### 2.5. Outcome Measures

Primary outcome measures:The usability and acceptability of the app will be assessed by both patients (end users) and clinicians (relevant stakeholders). In the patients, this is evaluated both objectively and subjectively. To obtain an objective feasibility result, we calculate the adherence with the app by dividing the number of completed assessments by the number of planned evaluations and provide the response rate. To obtain a subjective measure of usability and acceptability, at the end of the study period (3 months after the first use of the app), we administer the System Usability Scale (SUS) [31] using an online survey tool that will be sent by mail (*Qualtrics*).In the clinicians, the acceptability of the new app-based monitoring method is evaluated using an assessment protocol developed for a similar earlier study [16]. As reported in Appendix D, this includes items that are consistent with the technology acceptance model [32], including perceived utility, acceptability, and intended use. This will be evaluated at the end of the study with the *Qualtrics* online survey tool anonymously.

Secondary outcomes measures:

Assessed by the Pain Monitorapplication (all once daily from 7 p.m. to 9 p.m.):
Brace adherence: Ad hoc self-reported item: “When have you been able to wear the brace since you went to bed yesterday?” Response options cover all daily periods (morning only, afternoon only, only for sleeping, or any combination of these). To avoid bias due to socially desirable responses, honesty will be encouraged both during recruitment and in the informed consent.Treatment safety: An ad hoc question has been created including the most frequent side effects of brace use according to the literature [10,12] and the authors’ clinical expertise. These include: pain due to pressure, pain due to friction, excessive heat/sweating, movement difficulties, and being teased by peers or close ones.Clinical alarms: in addition to the assessment of brace adherence and side effects, several items were adapted from validated questionnaires (Appendix D) to assess pain intensity, unpleasant emotions, interference, avoidance, discomfort, and social support daily. Clinical alarms will be automatically generated and sent to the physicians by the app depending on the patients’ responses to these items (Table 1).

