## 3. Data Plan Analyses

Data are analyzed using intention-to-treat principles. Descriptive data (means, standard deviation, and frequencies) are reported for all study variables. These include usability and acceptability and response rates in the app (primary outcomes), together with brace adherence, the number of side effects, the number and type of clinical alarms generated by the app, stress, quality of life, perceived health status, and mood (secondary outcomes). Statistical differences between completers and non-completers are calculated. Completers are those who respond to at least 85% of the requested daily assessments, which is the average completion rate in EMA revealed in past meta-analytic research [42]. Adolescents who provide less than 85% responses to the app are considered non-completers.

Regarding feasibility, app adherence is calculated by dividing the number of responses registered in the app and the number of assessments programmed in the app (90 assessments, once daily during the whole study).

In relation to the clinical utility of the app, brace adherence is calculated by dividing the number of hours of use reported by the prescription they were given, as suggested in previous research [43]. Low brace adherence serves as a clinical alarm (Table 1). Changes in the remaining secondary measures (i.e., stress, perceived quality of life, perceived health status, and mood) from baseline to end of study are also explored, although it is expected to find minimal changes because these are not the main aim of the present study.

The results derived from the statistical analyses described above will be reported in the form of tables, graphs, and flowcharts. All the analyses are performed separately by the lead researcher and an independent researcher. An interim analysis is planned at the end of the study once 50% of the total sample has been evaluated. All coauthors and the Ethics Committee of the Vall d’Hebron University Hospital have access to these analyses and are allowed to participate in the decision to terminate the trial. The database is available under reasonable request for any researcher who requests it. Personal information from the participants is not included in this data set. The results from this feasibility study will be published anonymously in international journals and conferences.

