The present protocol described a feasibility study whose aim is to test the usability, acceptability, and clinical utility of an app-based system for the monitoring of adolescents with IS who use a brace. Specifically, we hope to provide new insights into the feasibility of the app (i.e., app adherence and usability), as well as into its utility in detecting non-compliance with brace (treatment adherence), brace-related side effects like pain and interference in sleep (treatment safety), and psychological distress associated with wearing the brace (i.e., intense unpleasant emotions and poor social support). Regarding feasibility, we expect to find high compliance rates with the app-based monitoring system in the end users. Non-adherence to the app will generate clinical alarms, so the professional will be able to contact the participants to encourage them to interact with the app. For this reason, we expect to find low attrition rates during the study period (90 days). Additionally, in relation to the feasibility results, we anticipate that the participants will be very satisfied with the app in terms of acceptability and usability (i.e., “I needed to learn many things before I could start using the system”). Based on previous similar research [45,46], we also anticipate that the clinicians will be satisfied with the app in terms of perceived utility, low burden, and high intention to use. Regarding the clinical utility of the app, we also hypothesized that the app would allow early detection of low brace adherence, brace-related side effects, and psychological distress associated with brace use. Ultimately, we expect that the early detection of these symptoms with the app-based monitoring system will allow clinicians to quickly detect and solve unwanted events and thus provide safer and more effective treatment. To our knowledge, this is the first study to test the feasibility and clinical utility of telemonitoring adolescents with IS through a multidimensional app.

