To what extent the app is useful for me as a professional?

To what extent the app can be useful for patients with IS?

To what extent the app with alarms is something I want to use in the future?

To what extent the app without alarms is something I want to use in the future?

To what extent the app alarms impacted daily job burden?

To what extent the app has an impact on burden (help patient downloading the app)?

2. **Items Assessed with the Pain Monitor Mobile Application**

A number of items were adapted from or developed considering well-established questionnaires (e.g., BSSQ, ISYQOL, SRS-22, HADS) in order to assess relevant brace-related domains namely side effects of the brace, avoidance behavior, discomfort, and social support.

Items assessed daily at evening

Please indicate if any of these possible consequences of the brace have been difficult for you to bear TODAY. You may select more than one option: (*Inspired by the SRS-22 and the ISYQOL*)

Pressure pain

Friction pain

Excessive heat/sweating

Movements difficulties

Teasing by peers or relative ones

None of the above have difficult for me today

Please indicate the intensity of your pain TODAY. Indicate the average for the whole day between 0 and 10. (*Inspired by the SRS-22*)

0 No pain ---------10 Extreme pain

Please indicate if you feel some of these intense emotions TODAY due to bracing. You may select more than one option: (*Inspired by the SRS-22 and the HADS*)

Sadness

Anxiety

Anger

Shame

Overwhelm

Frustration

I did not feel any of these emotions intensely because of the brace

Please indicate if brace have interfered you in some of these aspects TODAY. You may select more than one option: (*Inspired by the SRS-22, the ISYQOL, and the BSSQ*)

Sleeping (last night)

Basic movements

Friends’ relationships

Family’ relationships

Leisure activities

Academic activities

Mood

Dressing

Self-image

Motivation for going out (classroom or leaving home)

None of the above have disturbed me today

When have you been able to wear the brace sin you went to bed yesterday? [Item created to assess de degree of nonadherence (mildly vs. severe nonadherent), as recommended by [51]

Only at morning (8–14 h approx)

Only at afternoon (14–19 h approx)

Only for sleeping (last night)

Today at morning and afternoon, but no for sleeping (last night)

Sleeping (last night) and this morning

Sleeping (last night) and this afternoon

Sleeping (last night) and all day

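### The reported number of side effects is narrower than its label: it covers five listed effects that were hard to bear, leaves out sleep interference, and cannot record itching or any other unlisted effect

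*Protocol article*

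**What the plan says.** Section 2.5 (Outcome Measures) defines treatment safety as one ad hoc question on the most frequent brace side effects: "These include: pain due to pressure, pain due to friction, excessive heat/sweating, movement difficulties, and being teased by peers or close ones". The side-effects block of Table 1 lists the same five.

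Appendix D, part 2 (items in the Pain Monitor application) prints the question in full. Its stem is "Please indicate if any of these possible consequences of the brace have been difficult for you to bear TODAY". After the five effects the only remaining answer is "None of the above have difficult for me today".

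Section 3 (Data Plan Analyses) lists among the secondary outcomes "the number of side effects, the number and type of clinical alarms generated by the app", so the side-effect count is reported separately from the alarms and without any severity limit.

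Elsewhere the article describes side effects more widely. The Introduction gives as unwanted effects of bracing "e.g., pain, scuffing, or discomfort sleeping", and later imagines a patient who may "immediately stop wearing the brace when they experience pain or itching". The Discussion describes what the app should detect as "brace-related side effects like pain and interference in sleep (treatment safety", with sleep placed under the safety label.

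**The concern.** Detecting brace-related side effects is part of the stated clinical-utility aim, so readers will take the reported number of side effects as the total the app found. As the item is written, the figure has three limits that the label does not show:

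- It has a threshold. An effect that was present but not hard to bear that day is entered as none.
- It leaves out sleep interference, although the article's own account of treatment safety names it.
- It is a closed list. Itching, or any effect the authors did not list, has nowhere to go.

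The third limit differs in kind from the others. A threshold can be stated and a collected answer can be reclassified at analysis, but an effect that was never asked about cannot be recovered. Because Appendix D prints the item in full, condensation into an article does not explain the closed list, and a separate analysis plan could not repair it.

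**Working it through.** The point concerns an outcome definition, and the plan has no figure of its own to reproduce. The check is to take each effect the article names and ask whether it enters the side-effect count, and where else the daily survey or Table 1 would show it.

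| Effect | In the side-effect count? | Recorded elsewhere each day? | Alarm in Table 1 |
|---|---|---|---|
| Pressure or friction pain | Only if hard to bear | Yes: pain intensity 0–10 and discomfort 0–10, no threshold | Each effect 3 days; pain ≥3 for 3 days; discomfort ≥5 for 5 days |
| Difficulty moving | Only if hard to bear | Yes: basic movements in the interference item | 3 days in each item |
| Heat/sweating | Only if hard to bear | No second direct item | 7 days, from this item |
| Teasing | Only if hard to bear | No second direct item | 4 days, from this item |
| Sleep disturbance | No | Yes: sleeping (last night) in the interference item, no threshold | 3 days, call the patient |
| Itching | No | Not named; could show only indirectly | None of its own; discomfort ≥5 for 5 days or no brace use for 3 days might be reached |
| Any other unlisted effect | No | Not named; could show only indirectly | As for itching, if it causes discomfort or non-use |

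The rows fall into three groups.

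1. **Misclassified, not missing.** Sleep interference is collected daily, has an alarm, and enters the reported number and type of alarms. It is absent only from the side-effect count. Nothing in the article explains why movement appears in both the side-effect and interference items while sleep appears in only one.
2. **Thresholded, but with a second source.** Bearable pain and general discomfort appear on the 0–10 scales, and movement problems appear in the interference item.
3. **Not captured as such.** This group holds itching, other unlisted effects, and heat/sweating or teasing below the hard-to-bear level.

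On size, the documents give no frequency for any symptom. The following uses assumed rates only. Suppose each of the five listed effects is reported on 10% of days (5 × 0.10 = 0.50 reports per day), sleep interference occurs on a share s of days and itching on a share i.

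- Share of all such reports outside the side-effect count = (s + i) / (0.50 + s + i). With s = i = 0.05 this is 0.10 / 0.60 = 17%. With s = 0.30 and i = 0.20 it is 0.50 / 1.00 = 50%.
- Share not recorded as a named symptom anywhere (itching only) = i / (0.50 + s + i). With s = 0.30 and i = 0.05 this is 0.05 / 0.85 = 6%. With s = 0.05 and i = 0.20 it is 0.20 / 0.75 = 27%.

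The ranges are wide because the inputs are assumed. They show that the answer depends on frequencies the documents do not supply, and they are not estimates for this trial.

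**The case against.** The strongest reply is that the outcome is defined in section 2.5, not in the Discussion. Section 2.5, section 3, Table 1 and Appendix D agree on the five effects, and section 2.5 places interference among separate items. On this view the mismatch is one loose parenthesis. The list is said to rest on frequency in the literature and on clinical experience, and the team wanted a short survey. Itching is mentioned once, as an example. The outcome is secondary and descriptive in a 40-patient single-group feasibility study, and no stated decision rule depends on it.

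Much of this stands. The Discussion does not redefine the outcome, and whether itching is frequent enough for its own option cannot be judged from these documents.

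A reader might also infer that the trial as a whole under-counts harms, or that a patient with disturbed sleep every night would go unnoticed for 90 days. The documents do not support either. Three consecutive days of sleep interference raise an alarm recommending a call to the patient, and that alarm is reported. Troublesome itching could reach the discomfort alarm, or the non-use alarm if the brace were abandoned, though without its cause being identified. Nor does the Introduction's patient who puts up with discomfort necessarily answer none: someone can keep wearing the brace and still find it hard to bear.

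The reply does not remove the unstated threshold behind an unqualified label, or the lack of any place for an unlisted effect. A list of the most frequent effects is a reason to keep the list short, but not a reason to leave out a single catch-all option.

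**Conclusion.** The concern holds in a limited form. The secondary outcome is mislabelled and incomplete: it measures how many of five pre-listed effects were hard to bear that day, and it is reported as the number of side effects. For sleep this is a question of classification. For bearable pain, discomfort and movement problems it is a question of labelling, since other items record them. A true capture gap exists for unlisted effects such as itching, and for heat/sweating and teasing below the hard-to-bear level.

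The size of the undercount cannot be estimated from the documents. The primary outcomes (usability, acceptability and response rate) are unaffected. The conclusion assumes that Appendix D shows the side-effect item as it appears in the app, and that the count in section 3 is taken from that item, as section 2.5 implies. The change is worth making because it is cheap and because effects that were never recorded cannot be added later.

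**What to change.** Reconcile section 2.5, section 3, the Discussion, Table 1 and Appendix D in three steps.

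1. Include the sleeping (last night) answer from the interference item in the reported side-effect outcome, or show it beside that outcome, and say which. The data are already collected, so this is a wording change.
2. Add one answer to the side-effect item, 'Other problem caused by the brace', with short free text. This is a small app edit, a few seconds of response time, and brief coding at the end. If the app is already in use, give the date of the change and report this answer separately, because earlier records could not contain it. Whether it should raise an alarm is for the clinical team.
3. Report the outcome as 'side effects difficult to bear', so that the threshold in the question is visible in the result. This costs nothing.

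Steps 1 and 3 remain possible even if the app content can no longer be changed. In that case the report should say that effects outside the five listed could not be recorded.

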I was not able to wear the brace today

Please indicate how much have you avoided talking about your brace today. Rate from 0 to 10. (*Inspired by the BSSQ*)

0 I have not avoided it at all ------- 10 I have avoided it a lot

Please indicate how much have you avoided doing things you like or being with others to hide your brace today. Rate from 0 to 10 (*Inspired by the BSSQ*)

0 I have not avoided it at all ------- 10 I have avoided it a lot

Indicate from 0 to 10 the degree of discomfort with which you have worn the brace TODAY. (*Inspired by the ISYQOL*)

0 No discomfort ------- 10 Maximum discomfort

Select if you have lacked the support of any of these people regarding your brace TODAY. You may select more than one option: [*Inspired by the ISYQOL and the Brace Beliefs Questionnaire* [52]]

Friends

Family

Teachers

Other people

I felt supported today

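### Side effects, interference and discomfort are summarised without regard to same-day brace wear, so unworn days can pass as symptom-free days

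*Protocol article*

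**What the plan says.** Appendix D, part 2, prints the items that the app asks once a day. Four of them matter here.

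- **Side effects**, named in section 2.5 as the treatment-safety measure: "Please indicate if any of these possible consequences of the brace have been difficult for you to bear TODAY". The exit option is "None of the above have difficult for me today".
- **Interference**: "Please indicate if brace have interfered you in some of these aspects TODAY". It also has a single 'none' option.
- **Wear**: a list of day periods and combinations, ending with "I was not able to wear the brace today".
- **Discomfort**: "Indicate from 0 to 10 the degree of discomfort with which you have worn the brace TODAY". The scale runs from no discomfort to maximum discomfort.

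The wear item comes after the side-effect and interference items and before the discomfort item. No skip rule and no 'not worn' answer is shown for the other three.

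Section 3 plans means, standard deviations and frequencies for all study variables. The secondary outcomes it lists include "the number of side effects, the number and type of clinical alarms generated by the app". It states no link to wear for any of these. Table 1 defines alarms as runs of consecutive days, again with no wear condition. Pressure pain and no use of the brace each trigger after 3 days, and discomfort triggers at 5 or more on 5 days.

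The Introduction names unwanted effects as one of two explanations for non-compliance, and gives the example that "an adolescent may decide to immediately stop wearing the brace when they experience pain or itching".

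**The concern.** On a day without the brace, the easiest answers are 'none' and 0. These are also the answers of a patient who wore the brace all day without trouble. One means good tolerance and the other means no exposure, yet in the side-effect, interference and discomfort data they look the same.

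The protocol itself expects non-wear to depend on side effects. If patients with trouble wear the brace less, their unworn days lower the count of side effects and the mean discomfort. The error then runs towards apparent safety, and it is largest in the patients whom side effects may have driven off the brace. A secondary outcome labelled treatment safety would be partly a measure of how much the brace was worn. The Discussion offers the patient's physical and psychological state as a possible explanation of differences in adherence. A reader who compares symptom counts between good and poor wearers for that purpose could be misled.

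**Working it through.** No figure in the plan is in dispute. The check uses the 90 planned daily assessments (section 3) and the run lengths in Table 1. Wear patterns and symptom rates are assumptions, because the documents give none.

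**1. Dilution in general.** Let w be the share of answered days with any wear and p the share of worn days with a given symptom. Assume the patient answers 'none' on every unworn day. Then the rate over answered days is p × w.

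With p = 0.5:

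| w | rate over answered days | rate per worn day |
|---|---|---|
| 1.0 | 0.50 | 0.50 |
| 0.8 | 0.40 | 0.50 |
| 0.6 | 0.30 | 0.50 |
| 0.4 | 0.20 | 0.50 |

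The same tolerability per worn day looks better as wear falls.

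**2. Day-by-day patterns over 90 days.** Assume full response, pressure pain on every worn day, 'none' on every unworn day, and discomfort 6 when worn and 0 when not. The rate per worn day is then 100% throughout, and mean discomfort on worn days is 6.0.

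| days on / off | worn days | side effect, share of 90 days | mean discomfort, all days | longest symptom run | longest unworn run |
|---|---|---|---|---|---|
| 2 / 1 | 60 | 60/90 = 67% | 6 × 60/90 = 4.0 | 2 | 1 |
| 2 / 2 | 46 | 46/90 = 51% | 6 × 46/90 = 3.1 | 2 | 2 |
| 1 / 2 | 30 | 30/90 = 33% | 6 × 30/90 = 2.0 | 1 | 2 |
| 4 / 2 | 60 | 60/90 = 67% | 6 × 60/90 = 4.0 | 4 | 2 |
| 4 / 3 | 52 | 52/90 = 58% | 6 × 52/90 = 3.5 | 4 | 3 |

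**3. Alarms.** In the first three rows no symptom run and no unworn run reaches 3 days. The pressure-pain, discomfort and no-use alarms therefore stay silent for 90 days. With 4 on / 2 off the pressure-pain alarm fires. With 4 on / 3 off both it and the no-use alarm fire. Only gaps of 1 or 2 days can break a symptom run and also escape the no-use alarm, and then only if the worn stretches are short as well.

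**4. How little wear can escape the no-use alarm.** With n worn days there are at most n + 1 gaps. If no gap exceeds 2 days, they hold at most 2(n + 1) unworn days. So 90 − n ≤ 2(n + 1), which gives n ≥ 88/3 = 29.3. With full response, a patient who wears the brace on fewer than 30 of the 90 days must have a run of at least 3 unworn days and so must trigger the no-use alarm.

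**The case against.** The case on the other side is substantial, and much of it stands.

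- **Removal is not hidden.** The wear item records it the same day. Three consecutive days of no use lead to a recommended call, and partial wear does so after 7 or 15 days. A reader might infer that a patient who abandons the brace disappears as a safe case with the cause lost. The documents do not support that: the call is an opportunity to learn the cause, and earlier symptom reports stay on record.
- **Only single days are affected.** A reader might infer that someone who takes the brace off because it hurts is recorded as free of side effects. That does not follow. The items cover the whole day, so pain felt before a same-day removal can still be ticked, and worn days before removal still count.
- **Not every item presupposes wear.** Teasing, mood, self-image or residual pressure pain may be reported truthfully on an unworn day. Pain has its own item, worded without the brace: "Please indicate the intensity of your pain TODAY. Indicate the average for the whole day between 0 and 10". Only the discomfort item strictly requires wear. Setting all answers on unworn days to not applicable would delete genuine reports.
- **Section 3 is silent on scoring.** It does not say that unworn days count as symptom-free, and a denominator could be set in an analysis plan that is not shown. A total count over the monitored period is also a legitimate measure of burden.

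The item design remains. It is fixed in Appendix D and cannot be repaired by a denominator alone, because a 0 or 'none' on an unworn day needs a rule before it is summarised. The counts and the run rules, as stated, are also unconditional on wear.

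**Conclusion.** The point holds in a limited form. On unworn days the discomfort item has no valid answer, and the 'none' options of the side-effect and interference items do not tell tolerance from absence of exposure. Summaries that ignore wear can then make tolerability look better in poor wearers.

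The direction is clear if unworn days are mostly answered 0 or 'none'. The size is not known. The halving or more seen in some of the patterns above comes from assumed wear and symptom rates and should not be read as a forecast. The effect on alarms is narrow: intermittent gaps of 1 or 2 days only, and the reported alarm counts should be read with that in mind. The primary outcomes (usability, acceptability and response rate) are untouched. The change is worth making because a secondary safety outcome is exposed to a foreseeable bias and the data to correct it are already on the form.

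**What to change.** Add to section 3, or to the analysis plan:

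1. On days when the wear item records no wear, treat a discomfort score of 0 and 'none' answers on the side-effect and interference items as not applicable. Keep every positive report made on such days.
2. Beside the planned counts, report side effects, interference and discomfort per day with any wear and by same-day wear category, together with the share of unworn days. Show positive reports from unworn days separately, so that they are not lost from the per-worn-day figures.
3. Give a descriptive count of side-effect reports followed by a drop in wear category, with the time window fixed in advance.
4. State, next to the alarm counts, that an unworn day can interrupt a symptom run.

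A 'not worn today' answer in the app would make the data cleaner but is optional.

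The cost is some analysis wording and a recode of existing data, with no new collection. The downside is that poor wearers contribute fewer denominator days, so their per-day rates will be less precise.
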